## Abstract

**Background:**

Spasticity is the most common motor disorder in cerebral palsy (CP), and its management is complex, posing a significant challenge for the rehabilitation team. Radial extracorporeal shock wave therapy (rESWT) has emerged in recent years as an effective, non-invasive, and low-risk alternative for the management of spasticity in CP patients, with only minor side effects such as small bruises or discomfort during application. There is great variability in rESWT administration protocols, ranging from a single session up to the 12 sessions. The most extensively studied protocol involves 3 rESWT sessions with a one-week interval between session. According to current literature, the effect of rESWT has not been investigated by extending the time interval between sessions beyond 1 week to determine if therapeutic effects on spasticity can be prolonged over time.

**Methods:**

Following a power calculation using the minimal clinical important difference of our primary outcome (R2 of Modified Tardieu Scale), 72 patients will be included in the study. Enrolment is based upon inclusion/exclusion criteria outlined in the Methods section. Participants will be randomized in 3 groups. Each patient will receive 2000 impulses in the Triceps Sural muscle (distributed by all the plantar flexor muscles: soleus and gastrocnemius), at a 2.2 Bars pressure and a frequency of 8 Hz. The Control Group will receive 3 rESWT sessions with a time interval of 1 week between each session. The Experimental Group A will receive 3 rESTW sessions with a time interval of 2 weeks between each session and the Experimental Group B will receive 3 rESTW sessions with a time interval of 4 weeks between each session.

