## Introduction

1

Cerebral palsy (CP) is a neurological developmental condition that begins in early childhood and persists throughout life. It is defined as “a group of permanent disorders of movement and posture development, causing limitations in activity and attributed to non-progressive disturbances that occur in the fetal or infant brain development. Motor disorders in cerebral palsy are often accompanied by alterations in sensation, perception, cognition, communication, and behavior, as well as epilepsy and secondary musculoskeletal problems” (1). According to the data provided by the latest systematic review with meta-analysis available on the worldwide prevalence of CP, which includes forty-one regions across 27 countries on five continents, it is estimated that the prevalence of CP in high-income countries is 1.6 per 1,000 live births, while in low- and middle-income countries, it is 3.4 per 1,000 live births. CP remains the leading cause of childhood disability (2).

Spasticity is the most common motor disorder in CP (3). It is one of the signs of upper motor neuron syndrome and is characterized by an increase in stretch reflexes that varies depending on the speed of the stretching (4). Spasticity is a component of the multifaceted motor disability of CP, and although it may not be the primary factor interfering with function, participation, or activity (5), it can play an important role in limiting patients ability to mobilize and engage in daily activities by interfering with limb function, causing pain secondary to muscle spasms, which can disturb sleep (6, 7) and in the long term, lead fixed contractures and musculoskeletal deformities (8).

The management of spasticity in CP is complex and presents a great challenge for the rehabilitation team. There is considerable variation in the management of spasticity, including the availability of treatments (physical therapy, pharmacological interventions, orthopaedic interventions, surgical options, etc.) and the intensity of their use (9).

The objectives of his therapeutic approach include; reduce pain, facilitate the use of orthopaedic aids, improve posture, minimize contractures and deformity, facilitate mobility and dexterity, with the ultimate goal of maximizing the patient’s potential and promoting their independence and quality of life (10).

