### Outcome measures

2.7

Primary outcome measures: Spasticity of the treated muscles assessed with the Modified Tardieu Scale (MTS). Secondary outcome measures: Goal Attainment Scale (GAS), Timed Up and Go Test (TUG), 10 Meter Walk Test (10-MWT), Point shear wave elastography (pSWE), satisfaction with the therapy, and adverse effects. Prior to the first rESWT session, the blinded evaluating physiotherapist and his assistant will conduct a baseline assessment (t0) of all outcome variables and other aspects deemed appropriate as reference for assessing goal achievement. These assessments will be repeated across all intervention groups at 3 weeks from the start of treatment (t1), 5 weeks from the start of treatment (t2), 9 weeks from the start of treatment (t3), 12 weeks from the start of treatment (t4), and 24 weeks from the start of treatment (t5).

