#### Modified Tardieu Scale

2.8.1

The main variable of the study will be the physiological response of spasticity in the treated muscle, assessed using the Modified Tardieu Scale (MTS). This test is based on the evaluation of muscular resistance to passive stretching at two different speeds: slow speed (V1) and fast speed (V3), to quantify the joint angles at which such resistance appears. The V1 stretch is used to determine the angle of muscle resistance at low speed (R2), equivalent to the passive range of motion (pROM) and the V3 stretch is used to determine muscle resistance at high speed (R1) or catch reflex. The MTS it could be more sensitive than other measures in assessing spasticity. Its inter- and intra-rater reproducibility is acceptable (25). All measurements were conducted using a inclinometer to determine the angular value of the two segments. For the measurement of calf muscles, separate stretches were applied to the gastrocnemius muscle (measured with the knee extended) and the soleus muscle (measured with the knee flexed at 90°).

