### Sample size estimation

2.11

The sample size has been calculated using the GRANMO program, accepting an alpha risk of 0.05 and a beta risk of 0.2. It requires 24 subjects for each group, totaling 72 patients, to detect a difference equal to or greater than 5 degrees of improvement in R1 and R3 of MTS. It is assumed that the common standard deviation is 16.44, with a correlation coefficient between the initial and final measurement of 0.91. These data have been extracted from a study on the treatment of spasticity using shockwave therapy in patients with CP (21). A follow-up loss rate of 10% will be estimated.

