### Statistical analyses

2.12

Statistical analysis of the data will be conducted using SPSS software version 23 and R-software (MLMM package). An intention-to-treat analysis will be performed. Significance level 5% (*p*-value <0.05). For the descriptive analysis, a normality check will be conducted using Shapiro–Wilk / Kolmogorov–Smirnov tests. For quantitative variables, the mean and standard deviation will be reported (in case of non-parametric data, the median and interquartile range). For qualitative variables, frequency and percentages will be reported. For inferential statistics, a mixed linear model for repeated measures will be used and adjusted as necessary for covariates such as age, sex, GMFCS, and other comorbidities that may be observed. For the qualitative analysis, semi-structured interviews will be conducted, and the following categories will be established: Physical efficacy, bodily function (subcategories: increased relaxation, mobility, balance, etc.). Autonomy, daily life activities, and functionality (frequency, intensity, location). Pain conditions (intensity, location). Rating of satisfaction with shockwave therapy. Subjective, emotional, and related aspects.

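### The primary variable is R2 in the abstract, R1 and an undefined R3 in the sample size, and the unspecified Modified Tardieu Scale elsewhere, so the main test and its sample size cannot be tied to one angle

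*Protocol article*

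**What the plan says.** The article describes its primary variable in four places.

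- **Abstract, Methods:** the power calculation used the "minimal clinical important difference of our primary outcome (R2 of Modified Tardieu Scale". This is the only place where a single component is called primary.
- **Section 2.7, Outcome measures:** "Primary outcome measures: Spasticity of the treated muscles assessed with the Modified Tardieu Scale (MTS". No component is named.
- **Section 2.8.1, Modified Tardieu Scale:** "The main variable of the study will be the physiological response of spasticity in the treated muscle", assessed with the MTS. Again no component is singled out.
- **Section 2.11, Sample size estimation:** 24 per group is said to detect 5 degrees of "improvement in R1 and R3 of MTS", with a common SD of 16.44 and an initial-to-final correlation of 0.91.

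Section 2.8.1 defines two angles. The slow stretch (V1) serves "to determine the angle of muscle resistance at low speed (R2), equivalent to the passive range of motion (pROM". The fast stretch (V3) gives R1, the catch. The introduction describes spasticity as "characterized by an increase in stretch reflexes that varies depending on the speed of the stretching". Section 2.12 sets a single 5% significance level and plans a mixed linear model for repeated measures.

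**The concern.** The conflict is printed in the text; it is not a detail left to an analysis plan. Any analysis plan that names one angle will contradict at least one of the published statements.

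Three things are at stake.

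1. **What the trial tests.** The aim is longer benefit on spasticity. By the article's own definitions R2 is taken at slow speed only, so on its own it does not isolate the speed-dependent response. If R2 is primary, a positive result shows a change in passive range. The introduction itself lists passive range of motion and the MTS as separate outcomes of earlier studies.
2. **What the sample size supports.** One SD and one correlation serve two named angles, one of them undefined. A reader cannot tell whether 24 per group holds for R1, for R2 or for both.
3. **Error control.** If two angles are primary and either may carry the claim at 5%, the overall error rate exceeds 5%.

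**Working it through.** **Step 1. Can the statements be reconciled?** R3 could be a slip for R2, or a confusion with the fast stretch speed V3.

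| Reading of R3 | Section 2.11 then means | Abstract says | Agreement |
|---|---|---|---|
| Slip for R2 | R1 and R2, two variables | R2 only | No |
| Confusion with V3 | the fast-stretch angle, R1 | R2 only | No |
| A third angle | R1 plus an angle not defined in 2.8.1 | R2 only | No |

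No reading removes the conflict, and sections 2.7 and 2.8.1 do not settle it.

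**Step 2. Does the sample size reveal the angle?** Inputs from section 2.11: difference 5 degrees, SD 16.44, correlation 0.91, alpha 0.05, beta 0.20.

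- SD of the change score: 16.44 × √(2 × (1 − 0.91)) = 6.975.
- Per group, comparing mean change between two groups: n = 2 × [6.975 × (z for alpha + 0.842) / 5]².
- One-sided (z = 1.645): 2 × (6.975 × 2.486 / 5)² = 24.06, which matches the stated 24 to within rounding, before any allowance for loss.
- Two-sided (z = 1.960): 2 × (6.975 × 2.802 / 5)² = 30.55, so 31.

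The stated figure can therefore be reached from one SD and one correlation. Nothing in the arithmetic says which angle they describe. (Whether one-sided testing was intended is a separate question.)

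The angle matters because n is proportional to SD² × (1 − correlation). The article gives no second set of figures, so purely as an illustration keep the SD at 16.44 and assume another correlation for the other angle:

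- 0.95: 24.06 × 0.05 / 0.09 = 13.4 per group.
- 0.85: 24.06 × 0.15 / 0.09 = 40.1 per group.

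A modest difference between the angles would make 24 generous for one and inadequate for the other.

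**Step 3. What follows if R1 and R2 are both primary?** Assume no true difference and one omnibus group test per angle at 5%.

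- Bounds: 5% if the two tests always agree; 1 − 0.95² = 9.75% if they are independent.
- Simulation with 24 per group and a correlation of 0.5-0.8 between the angles: about 8-9%.
- If each angle were instead tested at 2.5%, with the same SD and correlation for both, the requirement would be 37 per group two-sided or 31 one-sided, before loss.
- If success required both angles, the error rate would not be inflated. With 80% power for each, power for both would lie between 0.8 × 0.8 = 64% (independent) and 80% (always agreeing).

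The article does not say which of these rules applies.

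**The case against.** The strongest reply is that R3 is a typing slip, that the abstract does name one component, and that muscle, visit, limb handling and order of comparisons are commonly left to an analysis plan that is not shown. Much of this stands. R3 probably is a slip, and those further choices are not errors in this document. But correcting the slip still leaves the abstract and section 2.11 with different primary variables, as Step 1 shows.

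A second reply is that R2 is a legitimate part of the MTS and that the introduction links spasticity to contracture and reports range gains alongside reduced spasticity. That is fair. A reader might infer that R2 can say nothing about the aim; the documents do not support so strong a statement. They support only that R2 by itself does not isolate the speed-dependent response.

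A reader might also count two angles, two muscles, five follow-up visits and three pairs of groups, which makes 2 × 2 × 5 × 3 = 60 tests, and infer a false-positive rate of 68-80%. That figure models separate t tests. Section 2.12 plans a repeated-measures mixed model, which takes the visits together, and nowhere says that each such comparison will be judged at 5%. Nor does the text say that the two legs of a bilateral patient will be analysed as independent units: section 2.6 says both are treated, and section 2.11 counts patients.

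**Conclusion.** The point holds as an internal contradiction about the primary variable. R2, R1 with an undefined R3, and the unspecified MTS cannot all be the variable on which the trial is powered and judged. It has to be resolved before the analysis, because it decides whether a positive result concerns spasticity or passive range, and whether 24 per group relates to the variable tested.

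The error inflation that can be put down to the contradiction itself is moderate: about 8-9% instead of 5%. This assumes that R1 and R2 are both primary, that either may succeed, that each gets one omnibus test at 5%, and that they correlate at 0.5-0.8. Higher rates depend on an analysis that the article does not state. The effect on power cannot be quantified from the document, because the source angle of the SD and correlation is not given.

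**What to change.** - Name one primary MTS angle in identical words in the abstract and in sections 2.7, 2.8.1 and 2.11. R1, the fast-stretch angle, best matches the article's own definition of spasticity; R2 would become secondary.
- Delete R3 or replace it with the angle intended.
- State which angle the SD of 16.44 and the correlation of 0.91 come from. If it is not the chosen primary angle, restate the basis of the sample size with figures for that angle.
- Should the sponsor want both angles as primary, say whether either or both must succeed, and set alpha and sample size to match.

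The primary muscle, time point, handling of bilateral limbs and order of group comparisons should also be fixed in advance, but these are the sponsor's choice and may sit in the analysis plan.

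The cost is wording in the protocol and registry entry, and R2 loses its place as the headline outcome. No new data are needed. If the SD and correlation prove to belong to another angle, the recalculated sample size could differ from 72.

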**Discussion:**

This study will provide further information regarding the effect of rESWT on spasticity in patients with CP. If an increase in the time interval between rESWT sessions allows for the prolongation of therapeutic benefits on spasticity, it will be clinically relevant fact. With the same treatment dosage, patients will be able to benefit from its effects for a longer period of time.

**Clinical trial registration:**

ClinicalTrials.gov, identifier NCT05702606.

## Introduction

1

Cerebral palsy (CP) is a neurological developmental condition that begins in early childhood and persists throughout life. It is defined as “a group of permanent disorders of movement and posture development, causing limitations in activity and attributed to non-progressive disturbances that occur in the fetal or infant brain development. Motor disorders in cerebral palsy are often accompanied by alterations in sensation, perception, cognition, communication, and behavior, as well as epilepsy and secondary musculoskeletal problems” (1). According to the data provided by the latest systematic review with meta-analysis available on the worldwide prevalence of CP, which includes forty-one regions across 27 countries on five continents, it is estimated that the prevalence of CP in high-income countries is 1.6 per 1,000 live births, while in low- and middle-income countries, it is 3.4 per 1,000 live births. CP remains the leading cause of childhood disability (2).

Spasticity is the most common motor disorder in CP (3). It is one of the signs of upper motor neuron syndrome and is characterized by an increase in stretch reflexes that varies depending on the speed of the stretching (4). Spasticity is a component of the multifaceted motor disability of CP, and although it may not be the primary factor interfering with function, participation, or activity (5), it can play an important role in limiting patients ability to mobilize and engage in daily activities by interfering with limb function, causing pain secondary to muscle spasms, which can disturb sleep (6, 7) and in the long term, lead fixed contractures and musculoskeletal deformities (8).

The management of spasticity in CP is complex and presents a great challenge for the rehabilitation team. There is considerable variation in the management of spasticity, including the availability of treatments (physical therapy, pharmacological interventions, orthopaedic interventions, surgical options, etc.) and the intensity of their use (9).

The objectives of his therapeutic approach include; reduce pain, facilitate the use of orthopaedic aids, improve posture, minimize contractures and deformity, facilitate mobility and dexterity, with the ultimate goal of maximizing the patient’s potential and promoting their independence and quality of life (10).

Several studies have demonstrated the favorable effect of extracorporeal shock wave therapy (ESWT) in the treatment of spasticity in patients with cerebral palsy, multiple sclerosis, traumatic brain injury, and stroke (11–14). Although the mechanism of action of ESWT remains unknown, current evidence suggests that it induces the production of nitric oxide, which modulates neurotransmission at neuromuscular junctions; triggers a cascade of biological responses, including the expression of angiogenesis-related growth factors, leading to an antifibrotic effect through increased blood flow and enhanced tissue regeneration; induces degeneration of acetylcholine receptors; and may selectively target the terminal plaques of neuromuscular junctions (15). Two types of extracorporeal shock waves are used in medical therapy; radial extracorporeal shock waves (rESW) and focused extracorporeal shock waves (fESW). Both are single acoustic impulses with an initial positive peak pressure between approximately 11 Megapascals (MPa) rESW and more than 100 MPa fESW, reached in less than 1 μs. There are no comparative studies on which of the two types of shockwave therapy, rESW or fESW, is more effective for addressing spasticity in patients with CP. However, there are comparative studies between these two therapies in the management of spasticity in stroke patients, where the results indicate that rESW may have a slightly better effect on the spasticity, and studies on rESW are of higher methodological quality and level of evidence (13).

Radial extracorporeal shock wave therapy (rESTW) has emerged in recent years as an effective, non-invasive, non-pharmacological and low-risk alternative for the management of spasticity in CP patients, with only minor side effects such skin redness or discomfort during application. Current literature agrees that rESWT treatment is effective in improving spasticity in individuals with CP; this effect has been studied primarily in the Triceps Surae or plantar flexor muscle. It has been shown that the effect of shock waves is maintained up to 12 weeks after treatment. Positive effects have been observed in the reduction of spasticity, leading to improvements in the Modified Tardieu Scale (MTS), in the Modified Asworth Scale (MAS), in the passive range of motion (pROM), in increasing of the Gross Motor Function Measurement (GMFM) and plantar support surfaces measured with force platforms, among others outcomes. Since rESWT is a relatively new approach for the management of spasticity, there is significant variability in administration protocols, particularly regarding the number of sessions (ranging from a single session to 12 sessions) and the time interval between sessions. The most extensively studied protocol involves 3 rESWT sessions with a one-week interval between each session. According to current literature, no study has conducted a follow-up longer than 12 weeks, and the effect of rESWT with extended time intervals between sessions beyond 1 week has not been investigated to determine whether the therapeutic effects on spasticity can be prolonged over time (16–24).

The aim of this study is to assess whether increasing the time interval between rESWT sessions extends the therapeutic benefits on spasticity to be prolonged in patients with CP.

## Methods and analysis (including design; selection/treatment of subjects; interventional methods; data analysis)

2

### Study design

2.1

This clinical trial is designed as a single-center randomized clinical trial with three parallel groups. This protocol follows the Consolidated Standards of Reporting Trials (CONSORT) Statement on randomized trials and it will be conducted according to the Recommendations for Interventional Trials (SPIRIT). A flowchart overview of the study is presented in Figure 1. The Standard Protocol Items: SPIRIT table for enrolment, interventions, and assessments is presented in Table 1.

**Figure 1 fig1:**
[figure not shown]
The flow diagram for this study. rESWT, radial Extracorporeal Shock Wave Therapy; MTS, Modified Tardieu Scale; GAS, Goal Attainment Scaling; TUG, Timed Up and Go Test; 10-MWT, 10 Meter Walk Test; pSWE, Point Shear Wave Elastography; X, Session of rESWT; W, Number Week.

**Table 1 tab1:** The standard protocol items: SPIRIT table for enrolment, interventions, and assessments.

	**Enrolment**	**Allocation**	**Intervention**					**Follow-up**	
Timepoint	-24 week	0	1 week	2 week	3 week	5 week	9 week	12 week	24 week
Enrolment									
Eligibility screen	x								
Informed consent	x								
Allocation		x							
Interventions									
CG			x	x	x				
EGA			x		x	x			
EGB			x			x	x		
Assessments									
MTS			x		x	x	x	x	x
GAS			x		x	x	x	x	x
TUG			x		x	x	x	x	x
10MWT			x		x	x	x	x	x
pSWE			x		x	x	x	X	x

Tabulation of enrolment, interventions, and assessments throughout the trial. CG – Control Group (3 rESWT sessions 1 week between each session). EGA - Experimental Group A (3 rESWT sessions 2 week between each session). EGB – Experimental Group B (3 rESWT sessions 4 week between each session). MTS – Modified Tardieu Scale. GAS - Goal Attainment Scaling. TUG - Timed Up and Go Test. 10MWT - 10 Meter Walk Test. pSWE - Point Shear Wave Elastography.

Seventy-two participants with cerebral palsy will be recruited. Patients will be randomized into 3 groups. All patients will be followed for 24 weeks. The trial was approved by the local medical and ethical commission (reference number PR-2021-16) and is registered in ClinicalTrials.gov (NCT05702606).

